### Exploratory outcomes

#### Objective 5 (exploratory)

16S ribosomal RNA (rRNA) gene V4 amplicon sequencing will be carried out on residual faecal DNA of eligible archived FIT study samples to characterise the faecal microbiome.

#### Objective 6 (exploratory)

The assessment of interval CRC’s will be examined after study end and during the passive follow-up period (Y4-Y7) in a subset of LS patients who had FIT negative results (< 6 μg/g f-Hb) throughout the course of the study (baseline + Y1-Y3).

### Monitoring

A mixture of on-site visits and central monitoring will be utilised throughout the life cycle of this trial. On-site visits will be conducted by the trial coordinator of the coordinating site, which will allow for the data to be verified against source documents, ensure essential documents are present in the Investigative Site File (ISF), and FIT kits have been delivered, stored, and dispensed appropriately. Centralised (remote) monitoring will be conducted by a named delegate of the Chief Investigator’s (CI’s) team and will allow the CI and Study Sponsor to maintain oversight of the trial. The central monitoring delegate will be listed on the trial delegation log, trained in Good Clinical Practice (GCP) and monitoring procedures specific to the coordinating site. Trial Management Group meetings will be held on a monthly basis to provide overall guidance and trial oversight.

Since the trial intervention, OC-Sensor™, is well characterised, non-invasive and of low risk, and tested as a supplemental modality to existing CRC surveillance practices for patients with LS, a Data Monitoring Committee has not been set up.

We do not anticipate any major safety concerns for the study, as faecal self-sampling using FIT kits has been safely performed in several other studies to date. Adverse events are therefore anticipated to be exceedingly minimal as the Clinical Laboratory Improvement Amendments (CLIA) waived FIT kit, OC-Sensor™, which will be utilised for the purposes of this research, is non-invasive and may be completed by participants in the comfort of their own home. Relatedly, serious adverse events (SAEs) are not anticipated and will therefore not be reported.

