Assuming approximately three quarters of the eligible 2745 LS patients are due for colonoscopy within the 18 month recruitment period (2745 × 0.75 = 2059), and in considering the projected response/uptake rate of ~ 63%, (which has since been observed in the same patient population as part of the continuing NHS England clinical service evaluation [18]), it is estimated that 1297 individuals will return a FIT sampling kit.

On aiming to recruit 400 Lynch Syndrome patients on surveillance (when considering existing available funding), we anticipate 352 (88%), will not have detectable advanced neoplasia and will be used to evaluate the specificity. Assuming true specificity of 94%, then the width of a 95% confidence interval will be approximately 5%. These numbers would also provide 87% power to show that the specificity is at least 90%. This is based on a one-sided one-sample score test of proportions with a 5% significance level using STATA/SE v. 17.0.

We will employ a modified intention-to-treat (mITT) approach whereby participants who return at least 1 FIT kit and have an outcome from colonoscopy are available for analysis. Participants whose colonoscopy result is unavailable are likely to be relatively uncommon when considering the high rate of colonoscopy surveillance adherence in this patient population [19, 20]. Nonetheless, we will report the frequency of those without colonoscopy and the frequencies of those returning 0, 1 or 2 FIT kits.

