F-Hb results to come from this study will not be directly disclosed to participants. Site Principal Investigator’s (PI’s) will receive electronic reports of f-Hb results if ≥6 μg/g study participants’ directly from the Southern Hub laboratory via NHS secure and encrypted emails in Years 1 and 3 (the intervening years between a study participant’s SOC colonoscopy) to inform triage for colonoscopy. FIT positivity in study participants will be determined by the limit of quantification (LoQ) at the pre-determined threshold of ≥6 μg/g f-Hb [22].

Although it is anticipated that only a small minority of study participants may meet criteria for an additional interval colonoscopy at Years 1 & 3 (approximately 10%, based on early data as part of a preceding emergency clinical service evaluation), those that are identified as “FIT positive” at the specified study periods will be contacted by their respective local PI to discuss their FIT results and advised to proceed with a colonoscopy which will be triaged via the NHS’ urgent two-week-wait (2WW) referral pathway.

Throughout the duration of the study, endoscopy and pathology reports will be securely sent from respective study sites to the coordinating centre for the abstraction of relevant outcome data which will be stored and managed within the FIT for Lynch REDCap database.

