## Discussion

As the implementation of our emergency national clinical service evaluation has elucidated thus far, the utility of FIT may present clinical value for patients with Lynch Syndrome as a means of non-invasive CRC surveillance in intervening years between colonoscopy, and as an efficient mechanism in risk-stratifying the highest risk patients within this patient population [18]. Though qualitative analysis is presently underway in understanding LS patient attitudes and perceptions towards this diagnostic device, the patient response rate (63%) exemplified a favourable response overall. Provided the short duration of this clinical service as an emergency measure to the COVID-19 pandemic, further investigation on the efficacy of this novel intervention is warranted and may be enabled by this longitudinal, multi-centre, prospective research study.

In addition to elucidating overall efficacy of FIT in patients with Lynch Syndrome, we aim to characterise the faecal microbiome of individuals with Lynch Syndrome (as outlined in Objective 4) through residual faecal DNA. The data to be collected from this study may facilitate deeper insights into the unique bacterial communities which reside in the microbiome of LS patients which may have important clinical implications. Moreover, we envisage subsequent versions of this protocol may allow for the assessment of cancer-associated genetic changes in human DNA from stool which have the potential to improve the accuracy of a microbiome-based test.

At the time of this writing, eleven NHS Trusts throughout England and Scotland have been included as study sites and active recruitment is underway. Nonetheless, we recognise that this study may present certain limitations or issues, such as the potential for additional colonoscopies during intervening years between biennial surveillance colonoscopies, which may be considered invasive and potentially cause harm to no benefit to the patient.

Considering the unique histopathology and morphology of LS-associated neoplasia (with a higher frequency of flat/subtle neoplasia) [25], the sensitivity of FIT may be lower in comparison to the FIT sensitivity rates depicted within population-based screening programmes. The rate of false positives findings may also be slightly elevated when considering for example the prevalence of anastomotic inflammation from previous CRC resection in this patient population.

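### The rule that serious adverse events are not reported rests on the safety of stool sampling alone and leaves out the extra colonoscopies that a positive study FIT triggers at Years 1 and 3

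*Protocol article*

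**What the plan says.** Three parts of the protocol article bear on this.

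**Monitoring.** The rule is that "serious adverse events (SAEs) are not anticipated and will therefore not be reported". The reason given is the nature of the kit: "We do not anticipate any major safety concerns for the study, as faecal self-sampling using FIT kits has been safely performed in several other studies". On similar grounds, "a Data Monitoring Committee has not been set up". The section does not mention the colonoscopy that may follow a positive result.

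**Results reporting and urgent colonoscopy triage, with the Table 1 footnote.** FIT results of 6 μg/g or more go to the site investigator "in Years 1 and 3 (the intervening years between a study participant’s SOC colonoscopy) to inform triage for colonoscopy". The investigator contacts the participant, who is to "discuss their FIT results and advised to proceed with a colonoscopy which will be triaged via" the two-week-wait pathway. The Table 1 footnote makes the Year 1 and Year 3 colonoscopies conditional on a FIT at or above 6 μg/g and on nothing else. The expected share of participants is "approximately 10%, based on early data as part of a preceding emergency clinical service evaluation".

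**Discussion.** The article lists the additional colonoscopies between biennial ones among the study's limitations, "which may be considered invasive and potentially cause harm to no benefit to the patient". It adds that some may be done by endoscopists unfamiliar with Lynch syndrome and may fall short in quality.

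**The concern.** The Monitoring section treats the study intervention as the sampling kit. In practice the intervention is the kit plus a referral rule. A participant with a positive FIT at Year 1 or Year 3 is advised to have an invasive procedure that the biennial schedule would not have given at that time. The protocol foresees harm from this step in one section. In another it declines to report serious events, on grounds that do not address the step.

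Two things are at stake. A serious complication of a colonoscopy that the study set in motion would not be reported. And when the study describes what annual FIT adds to biennial colonoscopy, lesions found would be presented without the complications of the procedures that found them.

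**Working it through.** **Inputs from the protocol article**
- Planned sample size: "On aiming to recruit 400 Lynch Syndrome patients on surveillance" (Study design).
- Share with an additional colonoscopy: about 10% (triage section). The text does not say whether this is per year or over Years 1 and 3 together.
- Rounds in which a positive FIT triggers referral: 2 (Years 1 and 3).
- Kit return in the preceding emergency service: 375/588, stated as 63.7% (Rationale for current study).

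The article gives no count of extra colonoscopies, so there is no stated figure to reproduce. The count has to be built from these inputs.

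**Number of study-triggered colonoscopies**

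Formula: participants × kit return × share positive × rounds. The number of rounds is set to 1 when the 10% is read as covering both years.

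| Reading of the 10% | All 400 return kits | 63.7% return |
|---|---|---|
| Total over Years 1 and 3 | 400 × 0.10 = 40 | 400 × 0.637 × 0.10 = 25.5 |
| Per round | 400 × 0.10 × 2 = 80 | 400 × 0.637 × 0.10 × 2 = 51.0 |

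Three cautions apply.
- All cells assume that everyone referred has the colonoscopy.
- The 63.7% is first uptake among people invited to the earlier service. The 400 here have already returned a baseline kit, because that return is what counts as consent. It is therefore a borrowed lower value and not a forecast for Years 1 and 3.
- The earlier service escalated at 10 μg/g, while this study refers at 6 μg/g. The article does not say which threshold the 10% belongs to. If it is the higher one, more participants would be positive here. As an assumed illustration, 15% per round with full return gives 400 × 0.15 × 2 = 120.

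**How many serious events this could mean**

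The article gives no complication rate, so one must be assumed. With 0.1% to 1% per procedure:
- 25 procedures at 0.1%: 25 × 0.001 = 0.025 expected events.
- 80 procedures at 1%: 80 × 0.01 = 0.8 expected events. The chance of at least one is 1 − 0.99^80 = 55%.
- 80 procedures at 0.1%: 1 − 0.999^80 = 7.7% chance of at least one.

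The study cannot estimate a complication rate with any precision. If none were seen, the one-sided 95% upper limit, 1 − 0.05^(1/n), would be 7.2% for n = 40 and 3.7% for n = 80. The case for recording events therefore rests on accountability for single events and on complete description, not on estimation.

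**Does anything else in the article cover complications?**
- The primary outcome, specificity, is assessed at Years 0 to 3. Participants referred at Years 1 and 3 have colonoscopy findings, so false-positive referrals can be counted.
- Endoscopy and pathology reports go to the coordinating centre throughout. They may show an immediate complication, but they cannot be relied on for events after discharge.
- No objective in Table 3 concerns procedural harm.

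Procedural complications are therefore the part left without a stated reporting route.

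**The case against.** **These colonoscopies are clinical care.** Table 1 marks them with the standard-of-care symbol, and the consultant makes the referral. That is a fair account of how they are delivered and paid for. It does not settle the point, because the same footnote says they take place only when the study FIT is positive. The study is the reason for them, whichever pathway carries them.

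**The article condenses a fuller protocol.** This protects it against a complaint about missing detail. The sentence at issue is a rule stated outright, with its reason, so it can be judged as it stands.

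**Harm is already measured.** A reader might infer that the main harm of the strategy goes uncounted. The documents do not support that. An unnecessary colonoscopy after a false-positive FIT is itself a harm, and the specificity outcome captures it. Only procedural complications are left out.

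**Table 2 has no complication field.** A reader might conclude that such data will not be collected. Table 2 is described as a summary of variables, so it does not show what the full case report form contains. The point rests on the Monitoring sentence alone.

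**Size.** A single figure of 80 is tempting, but it takes the 10% per round with full return. It is also tempting to add that 2 × 0.06 × 352 = 42 of the 80 would be in people without advanced neoplasia. That mixes two sources: 80 comes from 10% positivity and 42 from 94% specificity, which together leave 38 true positives. It also carries the recruitment-time share of 12% with advanced neoplasia into years that follow a standard-of-care colonoscopy. The article gives no basis for that, so the split should not be used.

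**Impact on the results.** No primary or secondary estimate changes, and few events are likely. This stands, and it limits the weight of the point.

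**Conclusion.** The point holds in limited form. The Monitoring rule rests on a rationale that omits the study-triggered colonoscopies, while the Discussion says those procedures may harm. The passages need to be reconciled.

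The number of procedures affected is in the tens: about 40 or 80 with full kit return, depending on how the 10% is read, and about 25 to 51 at a 63.7% return. It could be higher if the 10% belongs to the 10 μg/g threshold. The conclusion is the same on every reading.

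A reader might go further and infer that many serious events are expected, or that a monitoring committee is needed. The documents give no complication rate and support neither inference. What they do show is that a serious complication of a FIT-triggered colonoscopy would go unreported under the plan as written. This is worth correcting, but it does not threaten the accuracy results.

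**What to change.** Reconcile the Monitoring section, the triage section and the Discussion. Replace the blanket statement with wording such as: serious adverse events related to colonoscopies triggered by a study FIT at Year 1 or Year 3 are recorded and reported; none are anticipated from stool self-sampling itself.

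Add complication fields to the Year 1 and Year 3 case report form if it lacks them, for example perforation, bleeding and unplanned admission. Report the number of FIT-triggered colonoscopies and their complications descriptively beside the yield, without a formal test. State whether the 10% is per year or over both years, and which threshold it refers to.

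The cost is a little more abstraction from endoscopy reports that are already collected, and a query to sites about later events for some tens of procedures. The change goes through the amendment route described under Quality control and assurance. It alters what is recorded and leaves the referral rule untouched.

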### Quality control and assurance

Internal standard operating procedures will be strictly adhered to for the development, implementation, documentation, and analyses of the clinical trial. Moreover, all relevant regulations will be observed. Any proposed changes to the study conduct, design, or management will be notified to the original approving Research Ethics Committee (REC), and any other applicable regulatory authority via a substantial amendment. Changes to the study will not be implemented until a REC and any other relevant authority (e.g., Health Research Authority (HRA) amendment approval) has been obtained. Following REC approval, any approved study changes will be immediately communicated to the participating study sites and their respective Research & Development delegates for local approval and acknowledgement.

The study will comply with the General Data Protection Regulation (GDPR) which requires data to be anonymised / pseudo anonymised as soon as it is practical to do so. Identifiable fields will be removed and replaced with the participant’s unique Study ID. Identifiable data will not be included in the files provided for analysis.

The findings from this study will be made publicly available through publication or other dissemination tools without any unnecessary delay, and an honest and accurate transparent account of the study will be provided at that time.

## Discussion

As the implementation of our emergency national clinical service evaluation has elucidated thus far, the utility of FIT may present clinical value for patients with Lynch Syndrome as a means of non-invasive CRC surveillance in intervening years between colonoscopy, and as an efficient mechanism in risk-stratifying the highest risk patients within this patient population [18]. Though qualitative analysis is presently underway in understanding LS patient attitudes and perceptions towards this diagnostic device, the patient response rate (63%) exemplified a favourable response overall. Provided the short duration of this clinical service as an emergency measure to the COVID-19 pandemic, further investigation on the efficacy of this novel intervention is warranted and may be enabled by this longitudinal, multi-centre, prospective research study.

In addition to elucidating overall efficacy of FIT in patients with Lynch Syndrome, we aim to characterise the faecal microbiome of individuals with Lynch Syndrome (as outlined in Objective 4) through residual faecal DNA. The data to be collected from this study may facilitate deeper insights into the unique bacterial communities which reside in the microbiome of LS patients which may have important clinical implications. Moreover, we envisage subsequent versions of this protocol may allow for the assessment of cancer-associated genetic changes in human DNA from stool which have the potential to improve the accuracy of a microbiome-based test.

At the time of this writing, eleven NHS Trusts throughout England and Scotland have been included as study sites and active recruitment is underway. Nonetheless, we recognise that this study may present certain limitations or issues, such as the potential for additional colonoscopies during intervening years between biennial surveillance colonoscopies, which may be considered invasive and potentially cause harm to no benefit to the patient.

Considering the unique histopathology and morphology of LS-associated neoplasia (with a higher frequency of flat/subtle neoplasia) [25], the sensitivity of FIT may be lower in comparison to the FIT sensitivity rates depicted within population-based screening programmes. The rate of false positives findings may also be slightly elevated when considering for example the prevalence of anastomotic inflammation from previous CRC resection in this patient population.

Moreover, patients may perceive a negative (< 6 μg/g) FIT result as a conclusive finding which may potentially impact subsequent adherence to biennial colonoscopy for subsequent year(s). For this reason, FIT results will not be passed directly to the patient, though there is a possibility that participants may discern a negative FIT finding with the lack of a colonoscopy referral via the two-week wait (2ww) pathway in Years 1 & 3. It is also to be noted that any 2ww referred colonoscopies for eligible individuals in Years 1 & 3 may be conducted by a non-family cancer endoscopist, or someone unfamiliar with Lynch Syndrome and/or the research study, which may ultimately result in inconsistent or suboptimal colonoscopies. Despite the potential limitations in which FIT may pose throughout the duration of this study, colonoscopy alone may present constraints as well, such as the development of interval cancer(s) which may only be detectable at a later stage.

In considering the above, in addition to the known age, gene and gender-specific CRC risks that are observed within the LS population, we envisage FIT as an augmentative rather than a replacement modality with the potential to identify interval neoplasia and/or CRCs and it should therefore still be considered and further examined in this high-risk patient population. For these reasons, and in considering the breadth of this multi-Institutional research study, a concerted effort in standardising data collection is of utmost importance and has been prioritised by the research team.

## Data Availability

The dataset used and analysed during the current study will be made available from the corresponding author on reasonable request.

## Abbreviations

FIT: Faecal immunochemical test
CRC: Colorectal Cancer
CN: Colorectal Neoplasia
ACN: Advanced Colorectal Neoplasia
LS: Lynch Syndrome
SOC: Standard of Care
MMR: Mismatch Repair
EPCAM: Epithelial cell adhesion molecule
NHS: National Health Service
REC: Research Ethics Committee
HRA: Health Research Authority
SP: Study Participants
LoD: Limit of Detection
f-Hb: Faecal Haemoglobin
rRNA: Ribosomal Ribonucleic Acid
PI: Principal Investigator
CI: Chief Investigator
ISF: Investigative Site File
GCP: Good Clinical Practice
GDPR: General Data Protection Regulation
mITT: Modified Intention-To-Treat
CLIA: Clinical Laboratory Improvement Amendments
SAE: Serious Adverse Event
